## **STUDY PROTOCOL**

### **Study design**

The study will adopt a cluster randomized bioequivalence trial with four study groups; zinc, zinc in multiple micronutrients and multiple micronutrients without zinc (experimental groups adding once daily Micronutrient Powders (sprinklestm) to corn-soy porridge) and a comparator group on daily conventionally fortified Corn-Soy Blend (CSB).

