### **Randomization**

The sampling frame will consist of the 12 villages in Kiandutu slum. Three villages will be randomly allocated to each of the 4 study groups. Villages rather than study subjects will be randomized to avoid cross-contamination of information due of the close proximity of the study subjects. Computer generated randomization will be done by a statistician.

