### **Data analyses**

The field data will be cleaned and coded and analyzed using SPSS software. Socio-economic (SE) status data will be reduced by using principal components analyses to an index using STATA. ENA for SMART will be used to analyse anthropometric data. The indices used to determine nutritional status will be; WA, HA and WH. Nutritional status will be judged by the WHO standards. Child feeding practices will be assessed using the indicators as per WHO (2001b) and WHO (2007) IYCF guidelines. Child feeding index, breastfeeding and complementary feeding (initiation, meal frequency and dietary diversity as a proxy for quality) will be determined. Nutrient intakes will be analyzed using Nutri-survey. Relative risk and odds ratio will be used to show the association between morbidity patterns and zinc status. Pearson product moment correlation and chi-square will be used to determine the relationship between non-categorical variables (feeding practices and nutrition status, SE status) and categorical variables (sex, age, type of illness and maternal characteristics) with zinc status respectively.

The relationships between the categorical variables will be analyzed to assess inter-group differences in dietary practices, nutrition status, morbidity patterns and serum and hair zn status at baseline, monthly and end of the study using chi-square and t-test, ANOVA and ANCOVA. Simple linear regression will be used to determine the contribution of sprinkles/CSB, dietary practices and SE status to nutrition status, morbidity patterns and

serum zn levels. Multiple regression analysis will be used to determine the extent to which sprinkles/fortification, dietary practices and predict nutrition status, morbidity patterns and serum zn levels and logistical regression used to analyze for confounding variables. Content analysis will be used for qualitative data from FGDs by summarizing the information into emerging themes. Bioequivalence of sprinkles to CSB will be drawn if the percentages of children with serum zn  $<9.9 \mu\text{mol/L}$  is within  $\pm 20$  rule (excluding CRP levels  $>10 \text{ mg/l}$ ), the basis to accept or reject the null hypothesis. Significance will be determined at 95% confidence interval, P-value of 0.05.

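### Villages are randomised, but the between-arm comparisons are named as child-level tests with no allowance for village, so their p-values and intervals are too optimistic if outcomes cluster by village

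*Protocol*

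**What the plan says.** The Study design section states: "The study will adopt a cluster randomized bioequivalence trial with four study groups". The Randomization section adds "Three villages will be randomly allocated to each of the 4 study groups" and gives the reason: "Villages rather than study subjects will be randomized to avoid cross-contamination of information". The allocated unit is therefore the village, with 12 in all.

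The Data analyses section compares the arms on dietary practices, nutrition status, morbidity and serum and hair zinc "at baseline, monthly and end of the study using chi-square and t-test, ANOVA and ANCOVA". It continues: "Simple linear regression will be used to determine the contribution of sprinkles/CSB, dietary practices and SE status". It also plans multiple regression ("Multiple regression analysis will be used to determine the extent to which sprinkles/fortification, dietary practices") and "logistical regression used to analyze for confounding variables". The regression predictors are named, and village is not among them. The section mentions no mixed model, cluster-robust variance or village-level summary. Neither it nor the sample size section gives an ICC or a design effect.

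Bioequivalence is to be concluded when the percentages of children with serum zinc below 9.9 µmol/L agree within a ±20 rule, leaving out children with CRP above 10 mg/l. No interval method is attached to that rule. The only level the section states is 95% confidence, P = 0.05.

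**The concern.** Children in one village share their allocation, and plausibly their food preparation (the supplements are made in feeding centres), their surroundings and their exposure to infection. If their outcomes are correlated, the arm means vary more than a child-level test assumes, because chance differences between villages do not average out over only three villages per arm. The test then takes village variation for a treatment effect.

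This would affect every comparison of arms on zinc status, growth and morbidity. Arms would be declared different too often, and reported intervals would be too short. The protocol does not merely leave the method open. It names methods that, in standard form, do not fit its own allocation, and a later analysis plan that followed it would inherit the mismatch.

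**Working it through.** **Inputs from the protocol.** Three villages per arm and four arms (Randomization); 67 children per arm before the attrition allowance, 80 with it (sample size section); two-sided 5% level (Data analyses). The 67 is taken as stated. The printed equation does not return it: (1.64 + 1.28)² × 0.71² / (0.2 − 1.0)² = 8.526 × 0.504 / 0.64 = 6.7. That is a separate matter and does not affect this point.

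**Assumptions not in the protocol.** ICC of 0.01, 0.02 or 0.05, and equal village sizes.

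**Step 1: design effect.** Children per village m = 67 / 3 = 22.3. For a factor constant within village, such as arm, DE = 1 + (m − 1) × ICC = 1 + 21.33 × ICC.

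**Step 2: true size of a nominal 5% pairwise test.** 2 × [1 − Φ(1.96 / √DE)].

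**Step 3: true size of a nominal 5% four-arm test.** P(χ² on 3 df > 7.815 / DE).

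| ICC (assumed) | DE | √DE | 1.96/√DE | Pairwise error | 7.815/DE | Four-arm error |
|---|---|---|---|---|---|---|
| 0 | 1.00 | 1.00 | 1.96 | 5.0% | 7.82 | 5.0% |
| 0.01 | 1.21 | 1.10 | 1.78 | 7.5% | 6.44 | 9.2% |
| 0.02 | 1.43 | 1.19 | 1.64 | 10.1% | 5.48 | 14.0% |
| 0.05 | 2.07 | 1.44 | 1.36 | 17.3% | 3.78 | 28.6% |

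**Step 4: check by simulation.** 20,000 null trials with beta-binomial village prevalences and three villages of 22 children per arm. At an assumed overall prevalence of 30%, the child-level chi-square rejected in 7.7%, 10.1% and 17.1% of trials (pairwise) and 9.1%, 13.7% and 28.2% (four-arm) at the three ICCs. At 20% prevalence, the protocol's expected figure for two of the arms, it rejected in 7.6%, 10.1% and 17.4%, and in 9.2%, 13.7% and 28.6%. The choice of prevalence hardly matters. A one-way analysis of the 12 village proportions held 4.9% to 5.2% throughout.

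**Step 5: sensitivity to village size.** With all 80 children per arm, m = 80 / 3 = 26.7 and the pairwise errors become 8.0%, 11.1% and 19.5%.

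**Step 6: how much wider a village-based 95% interval is.** With the four arms pooled there are 12 − 4 = 8 residual df and t = 2.306. The width relative to the child-level interval is √DE × 2.306 / 1.96: 1.30, 1.41 and 1.69 at the three ICCs. If only the two arms being compared are used (4 df, t = 2.776), it is 1.56, 1.69 and 2.04.

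**The case against.** **The protocol never says that children are independent.** This is true. ANOVA, ANCOVA and regression can be run on village summaries or with a village term, and a separate analysis plan might say so. But the protocol lists the regression predictors without village and names chi-square and t-test with no such qualification. A reader following it would run child-level tests. The objection limits how absolutely the point may be put, but does not remove it.

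**The size rests on an ICC the protocol does not supply.** This also stands. At an ICC of zero there is no inflation, and the figures above are conditional. The direction holds for any positive ICC.

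**Not every planned analysis is affected in this way.** A reader might infer that all the tests in the section fail. The section also plans correlations, relative risks, odds ratios and chi-square tests relating sex, age, illness or morbidity to zinc status. Those factors vary within villages, so the design effect used here does not carry over to them, and they are less affected.

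**A rate of false bioequivalence cannot be read off the plan.** It is tempting to quote one by assuming a two one-sided tests procedure with a 90% interval. The protocol contains no such procedure, only a ±20 rule on percentages. Read literally as a rule on observed percentages, it would pass about half of trials with a true 20-point difference whether or not outcomes cluster (51 to 53% in simulation), so clustering does not drive that error.

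**Village is not inseparable from arm.** Villages are nested in arms with three replicates each, so between-village variance can be estimated, on 8 df. The remedy relies on this.

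**Conclusion.** The point holds for comparisons between randomised arms. The stated design allocates villages, while the stated tests, in standard form, analyse children and leave between-village variation out of the error term. With about 22 children per village and assumed ICCs of 0.01 to 0.05, the true error of a nominal 5% test is about 7.5% to 17% for a pairwise comparison and about 9% to 28% for a four-arm comparison. Correct standard errors are 1.10 to 1.44 times those a child-level analysis would report. The figures assume equal village sizes.

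For bioequivalence the supported conclusion is narrower: any child-level interval used to apply the ±20 rule would be too short when the ICC is positive, and the effect on the decision cannot be sized until the interval is defined. The point should be settled before analysis, because p-values obtained as the plan now reads could not support conclusions about differences between arms.

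**What to change.** State in the Data analyses section that all between-arm comparisons are made by village.

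- **Low serum zinc (binary).** Take the proportion below 9.9 µmol/L in each village, fit a one-way model to the 12 values (8 residual df), report t-based intervals for arm differences, and judge the ±20 margin against that interval.
- **Continuous outcomes.** Use village means in the same way, or a linear mixed model with a village random intercept, plus a child intercept for monthly measures, and Satterthwaite or Kenward-Roger degrees of freedom. That linear-model option is not meant for the binary zinc outcome.
- **Avoid** large-sample robust standard errors with three villages per arm. Avoid also a permutation test of three villages against three: there are 20 arrangements, so the smallest two-sided p is 2/20 = 0.10.

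One check on the pooled model: the protocol expects prevalences of 20%, 10%, 20% and 50%, so p(1 − p) runs from 0.09 to 0.25 and averages (0.16 + 0.09 + 0.16 + 0.25) / 4 = 0.165. For the arm without zinc against CSB the relevant average is (0.25 + 0.16) / 2 = 0.205, so pooling would somewhat understate that contrast's variance. A two-arm analysis on 4 df is a sensible sensitivity check there.

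**Cost.** New analysis wording, a village identifier in the data, and wider intervals. As an illustration, take 20% prevalence in both arms, 67 children each and a 95% interval. The standard error is √(2 × 0.2 × 0.8 × DE / 67), and the half-width on 8 df is 2.306 times that: 17.6, 19.0 and 22.9 percentage points at ICC 0.01, 0.02 and 0.05. A child-level interval would show 1.96 × 6.91 = 13.5. At an ICC of 0.05 an interval of the expected width could not fit inside ±20 even with identical arms. That limit comes from the design, and the child-level analysis would only conceal it.

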### 3.4.6 Sample size determination

Determination of sample size will be based on the primary objective and the formula by Liu

& Chow (1992). Where; 
$$n = \frac{(Z_{\alpha} + Z_{\beta})^2 \sigma^2}{(\delta - \varepsilon)^2} = \frac{(1.64 + 1.28)^2 0.71^2}{(0.2 - 1.0)^2} = 67$$

Where; n = No. of study subjects per group,  $\sigma$  = variance within the groups,  $\delta$  = expected outcome difference of the groups (20 % as per the bioequivalence rule),  $\varepsilon$  = the absolute values of proportion differences among the groups. The standard normal deviate at the required confidence interval (95 probability error).

The prevalence of zinc deficiency in Kenya is 50% (GOK & UNICEF, 2008). The estimated post-intervention prevalence of 20%, 10%, 20% and 50% for the reference, ZN, ZN in MMN and MMN without ZN groups respectively. To show equivalence within 20% rule with 80% power and 5% significance, a sample size of 67 per group was obtained and allowing 20% attrition, a sample size of 80 per group is obtained.

Where; n = The desired sample size, z = The standard normal deviate at the required confidence interval (95 probability error equal to 1.96), p = The proportion of occurrence of the phenomenon (0.5) since prevalence is 50%, q = The proportion of non-occurrence is (1-P) = 0.5, d = level of statistical significance (0.05 for 95% level of significance).

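### The ±20 equivalence limit has no unit where the decision rule is stated; on the percentage-point scale that the sample size implies, it allows two thirds of the expected zinc effect to be lost

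*Protocol*

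**What the plan says.** The protocol has one criterion for its main conclusion, in Data analyses: "Bioequivalence of sprinkles to CSB will be drawn if the percentages of children with serum zn" below 9.9 µmol/L lies within ±20, leaving out children with CRP above 10 mg/l. The same sentence makes this the ground for accepting or rejecting the null hypothesis. It gives no unit for the 20. It also does not say whether the observed percentages or a confidence interval must fall inside the limits. The 95% confidence level in the following sentence is not tied to them.

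Section 3.4.6 uses the same rule to size the trial. It defines δ as the "expected outcome difference of the groups (20 % as per the bioequivalence rule"), enters it as 0.2, and subtracts from it ε, defined as "the absolute values of proportion differences among the groups". The planning figures are: "The estimated post-intervention prevalence of 20%, 10%, 20% and 50% for the reference, ZN, ZN in MMN and MMN without ZN groups respectively". The starting level is also given: "The prevalence of zinc deficiency in Kenya is 50" per cent. The aim is put as "To show equivalence within 20% rule with 80% power and 5% significance", and the result as "a sample size of 67 per group was obtained and allowing 20% attrition, a sample size of 80 per group is obtained".

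**The concern.** When the endpoint is a percentage, a limit of 20 can mean 20 percentage points or 20% of the reference value. These are very different rules when the reference is expected to be 20%. On the plan's own figures they give opposite verdicts for the zinc-only arm. An unstated scale could also be settled after the endline results are known.

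A second question follows once percentage points are taken as meant. The protocol gives no reason for the margin beyond calling it the bioequivalence rule. The margin needs to be set against the effect it is supposed to protect, because that decides what a finding of bioequivalence would mean for a reader choosing between sprinkles and CSB.

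**Working it through.** **Inputs, all from section 3.4.6:** expected endline deficiency of 20% (CSB), 10% (zinc), 20% (zinc in micronutrients) and 50% (micronutrients without zinc); starting prevalence 50%; margin 0.2; z values 1.64 and 1.28; σ 0.71; 67 evaluable children per group.

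**1. The plan's own figure.** The printed formula gives (1.64 + 1.28)² × 0.71² / (0.2 − 1.0)² = 8.526 × 0.504 / 0.64 = 6.7, not 67. With ε = 0.1 (10% versus 20%) it gives 8.526 × 0.504 / 0.01 = 430. The nearest reconstruction is equivalence of two proportions, both at 20%, with an absolute margin of 0.20:

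n = (1.64 + 1.28)² × (0.16 + 0.16) / 0.20² = 8.526 × 0.32 / 0.04 = 68.2,

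which is close to 67. A relative margin of 20% at a reference of 20% is 0.04 in absolute terms: 8.526 × 0.32 / 0.04² = about 1,705 per group. The planned size therefore fits percentage points and cannot fit a relative limit.

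**2. Verdicts on the plan's expected results, CSB at 20%.** Relative limits: 20 × 0.8 = 16% to 20 × 1.2 = 24%. Percentage-point limits: 20 − 20 = 0% to 20 + 20 = 40%.

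| Arm | Expected | Difference | Points | Relative |
|---|---|---|---|---|
| Zinc | 10% | −10 points (−50%) | inside | outside |
| Zinc in micronutrients | 20% | 0 | inside | inside |
| Micronutrients without zinc | 50% | +30 points (+150%) | outside | outside |

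Only the zinc arm changes verdict. On the relative scale it fails by being better than CSB, but the rule as written is two-sided, so it still fails.

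**3. What the percentage-point margin gives up.** Expected CSB effect: 50 − 20 = 30 points. Margin as a share of it: 20/30 = two thirds. A product at the limit leaves 40% deficient and achieves (50 − 40)/(50 − 20) = 10/30 = one third.

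**4. How often such a product would pass.** Exact binomial enumeration, 67 per arm, CSB truly at 20%, independent children, limits ±20 points:

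| True rate in test arm | Observed percentages only | 90% interval inside | 95% interval inside |
|---|---|---|---|
| 40% | 0.51 | 0.05 | 0.02 |
| 20% | 0.996 | 0.79 | 0.65 |
| 10% | 0.95 | 0.51 | 0.39 |

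Under a relative limit on observed percentages, the arm at 10% would pass with probability 0.12, against 0.95 in percentage points.

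**5. Check by normal approximation, two one-sided tests at 5%.** At 20% versus 20%: SE = √(2 × 0.2 × 0.8/67) = 0.069; power = 2Φ(0.20/0.069 − 1.645) − 1 = 0.79. At 10% versus 20%: SE = √((0.09 + 0.16)/67) = 0.061; the nearer limit is 0.20 − 0.10 = 0.10 away, so power = Φ(0.10/0.061 − 1.645) = about 0.50. Both agree with the 90% interval column.

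**The case against.** The strongest reply is that the protocol does have a scale. Section 3.4.6 subtracts an absolute difference in proportions from 0.2, which makes sense only in percentage points, and the planned size agrees. This stands. A reader might infer that the whole protocol leaves the limit without a scale; it does not. The missing unit is in the decision rule, and the relative reading is the less likely one. The repair is still needed. The words used in 3.4.6 are 20% and a bioequivalence rule, which do not exclude a relative limit, and the formula that carries the scale does not give its printed result.

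Three further inferences are tempting and do not hold.

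- *The rule accepts a product with one third of the effect.* This is the case exactly on the margin. Such a product passes about half the time only if observed percentages are compared. With a 90% interval it passes about 5% of the time, as a 5% test should allow. The protocol does not say which applies, and that silence is part of the point.
- *The lower limit can never be crossed, so the rule tests one side only.* The 20% for CSB is a planning estimate: if CSB ends at 30%, the lower limit is 10%. Under an interval rule the lower side matters even at 20%. Two-sided power there is 79%, against Φ(0.20/0.069 − 1.645) = 89% for one side alone.
- *The margin should be cut, for example to 15 points, half of the expected effect.* Nothing in the protocol supports that figure. By the formulas in step 5, power would fall to about 40% at 20% versus 20% and about 20% for the zinc arm at 10%.

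**Conclusion.** The point holds in a limited form. The sentence that decides equivalence lacks a unit and does not say whether an interval must lie inside the limits. Section 3.4.6 implies percentage points, so this is a defect in how the criterion is stated and not evidence that no scale was intended. The scale matters: the expected zinc-arm result of 10% against 20% is inside one set of limits and outside the other.

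On the implied scale the margin equals two thirds of the expected 30-point effect, so meeting it supports retention of at least one third of that effect. Unqualified bioequivalence says more than that.

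These sizes assume that deficiency without zinc stays at 50%, as the plan expects for micronutrients without zinc, and that CSB ends at 20%. The probabilities assume 67 evaluable children per arm after the CRP exclusion and ignore the randomization of three villages per arm. Clustering would lower the power of an interval rule that allows for it.

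**What to change.** Before any endline zinc result is seen, amend section 3.4.6 and Data analyses to say that:

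1. the limit is an absolute difference of 20 percentage points from CSB in the proportion of children with serum zinc below 9.9 µmol/L;
2. the confidence interval for that difference, and not only the observed percentages, must lie wholly within the limits, with its level named (a 90% interval corresponds to two one-sided tests at 5% and to the 1.64 in the sample size formula);
3. the conclusion, if the criterion is met, reads: *deficiency prevalence within 20 percentage points of CSB, which on the planning figures preserves at least one third of the expected effect*, in place of unqualified bioequivalence.

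The change is one of wording and leaves design and sample size alone. The first cost is a weaker claim. The second is that the interval requirement makes the power explicit. With a 90% interval it is about 79% at 20% versus 20%, but only about 50% for the zinc arm at its expected 10%. With a 95% interval the figures are about 65% and 39%. All are before clustering.

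### The single 80% power claim does not hold for zinc-only sprinkles against CSB: on the protocol's own expected rates that contrast has about 50% power, and the contrast that carries the bioequivalence conclusion is not named

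*Protocol*

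**What the plan says.** The Study design section describes three experimental groups that add sprinkles to corn-soy porridge (zinc; zinc in MMN; MMN without zinc) and "a comparator group on daily conventionally fortified Corn-Soy Blend (CSB").

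Section 3.4.6 (Sample size determination) lists the expected results: "The estimated post-intervention prevalence of 20%, 10%, 20% and 50% for the reference, ZN, ZN in MMN and MMN without ZN groups respectively". It then states: "To show equivalence within 20% rule with 80% power and 5% significance, a sample size of 67 per group was obtained". The margin is described as "expected outcome difference of the groups (20 % as per the bioequivalence rule") and enters the equation as 0.2. The term ε is defined as "the absolute values of proportion differences among the groups". No pair of groups is named for the power claim.

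The Data analyses section gives the decision rule: "Bioequivalence of sprinkles to CSB will be drawn if the percentages of children with serum zn" below 9.9 µmol/L are within a ±20 rule, after excluding children with CRP above 10 mg/l. It names no sprinkles group and sets significance by a 95% confidence interval.

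Table 1 gives 5 mg zinc to Group 1 (zinc only), Group 2 (zinc in MMN) and CSB. Group 1 contains nothing else. CSB also carries iron, calcium, and vitamins A, C and several of the B group.

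**The concern.** Power to show equivalence depends on how far the expected true difference lies from the margin. The protocol expects no difference between zinc in MMN and CSB, but a 10-point difference between zinc only and CSB, which is half of the 20-point margin. One sample size cannot give both contrasts the same power, yet one figure is stated.

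If zinc only v CSB is among the comparisons meant, the trial could fail to show equivalence there about half the time even when every planning assumption is correct. The two products also differ in co-nutrients as well as in delivery. A failure could then be misread as sprinkles delivering zinc less well, although the protocol expects fewer deficient children in that arm than with CSB.

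**Working it through.** **Inputs.** From section 3.4.6: expected deficiency 20% (CSB), 10% (zinc only), 20% (zinc in MMN); margin 0.2, read as 20 percentage points; 67 per group, 80 after attrition; critical values and σ as in "1.64 + 1.28)^2 0.71^2". From Data analyses: 95% interval. From Randomization: three villages per group. No intracluster correlation (ICC) is given.

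**The protocol's own figure.** The equation as printed gives

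(1.64 + 1.28)² × 0.71² / (0.2 − 1.0)² = 8.526 × 0.504 / 0.64 = 6.7, not 67.

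The printed ε of 1.0 matches none of the expected differences from CSB (0, 0.10, 0.30). Keeping the printed Z values, some alternatives are:

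- σ = 0.71, ε = 0.1: 8.526 × 0.504 / 0.01 = 430
- σ = 0.71, ε = 0: 8.526 × 0.504 / 0.04 = 107
- 20% v 20%, variance 0.16 + 0.16 = 0.32, ε = 0: 8.526 × 0.32 / 0.04 = 68

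Only the last comes near 67, and it does not use the printed σ.

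**Power at 67 per group.** For two one-sided tests with margin m = 0.2 and absolute expected difference d:

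SE = √[(p₁q₁ + p₂q₂)/n]

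Power = Φ[(m − d)/SE − z] + Φ[(m + d)/SE − z] − 1, with z = 1.645

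- *Zinc in MMN v CSB (20% v 20%):* SE = √(0.32/67) = 0.0691. Each side: 0.2/0.0691 − 1.645 = 1.249, Φ = 0.894. Power = 2 × 0.894 − 1 = 0.788.
- *Zinc only v CSB (10% v 20%):* SE = √[(0.09 + 0.16)/67] = 0.0611. Near side: 0.1/0.0611 − 1.645 = −0.008, Φ = 0.497. Far side: 0.3/0.0611 − 1.645 = 3.27, Φ = 0.999. Power = 0.496.

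Simulation of binomial counts gives 79.0% and 50.7%, so the normal approximation is adequate.

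**Sensitivity**

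| Setting | Zinc in MMN v CSB | Zinc only v CSB |
|---|---|---|
| n = 67, one-sided 5% | 79% | 50% |
| n = 80, one-sided 5% | 87% | 56% |
| n = 64 (80 less 20%), one-sided 5% | 76% | 48% |
| n = 67, 95% interval | 65% | 37% |
| n = 67, one-sided 5%, assumed ICC 0.01 | 67% | 43% |
| n = 67, one-sided 5%, assumed ICC 0.02 | 56% | 39% |
| n = 67, one-sided 5%, assumed ICC 0.05 | 29% | 27% |

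The clustering rows use a design effect of 1 + (67/3 − 1) × ICC, that is 1.21, 1.43 and 2.07. The ICC values are assumptions for illustration.

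**Size needed.** For 80% power, zinc only v CSB needs 0.25 × (1.645 + 0.842)² / 0.1² = 155 per group, or 197 with a 95% interval, before attrition and clustering.

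**The case against.** **The rule names no arm.** Data analyses says only sprinkles. Taken literally that includes the zinc-free group, whose expected 50% lies 30 points from CSB and outside the margin, so the authors may not have meant every arm. Contrasts may also be fixed in an analysis plan that is not shown. This stands as a reason not to assert that the zinc-only arm is definitely tested. It does not rescue the power statement, which is in the protocol, follows a list of unequal rates and is unqualified.

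**The rule may concern point estimates.** If bioequivalence only requires the observed percentages to lie within 20 points, zinc only v CSB would pass about 95% of the time. But section 3.4.6 claims a 5% significance level, and a point-estimate rule does not provide one: a true difference equal to the margin would pass about half the time.

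**Stronger readings that the documents do not support.**

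- A reader might infer that the 80% was calculated for 20% v 20%, because that variant gives 68. The text does not say so. The printed σ² of 0.504 is close to 2 × 0.5 × 0.5, the variance at 50% prevalence, and not 0.32. The agreement may be chance.
- A reader might infer that CSB is a matched comparator for Group 2 and an invalid one for Group 1. Table 1 shows that Group 2 differs from CSB too: iron 12.5 v 8 mg, folic acid 160 v 50 mcg, thiamine 0.5 v 0.1 mg, no calcium against 100 mg, and vitamins E, B6 and D3, iodine and copper in Group 2 only. Group 2 is the closest match, no more.
- A reader might take the expected 10% v 20% as the size of a co-nutrient effect, and so of a bias. The protocol never says why it expects those rates.
- A reader might conclude that zinc only v CSB should carry no claim at all. Comparing two products of different composition is legitimate if that is the question. It cannot by itself assign a difference to delivery.

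**Conclusion.** The stated 80% power does not apply to zinc only v CSB. On the protocol's own rates, margin and sample size the power is about 50%, against about 79% for zinc in MMN v CSB, a gap of 29 points. The printed equation supports 80% for neither.

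These figures assume an absolute 20-point margin, a confidence-interval (two one-sided tests) criterion, 67 evaluable children per group and independent children. The 95% interval, the CRP exclusion and any village correlation lower them; 80 evaluable children raises zinc only v CSB to 56%. If the margin were relative, it would be 0.2 × 20 = 4 points and the expected 10-point difference would lie outside it.

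On composition the conclusion is limited. Zinc only v CSB differs in co-nutrients and delivery together, so it needs careful interpretation, and the decision rule should say which contrast it uses. The documents do not establish that the comparison is biased by any particular amount.

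**What to change.** In section 3.4.6, give power separately for each zinc-containing sprinkles arm against CSB: about 79% for zinc in MMN and about 50% for zinc only at 67 per group, both before clustering. Do not present 80% as applying to zinc only v CSB. Correct the equation, or replace it by one whose inputs and result agree.

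In Data analyses, name the contrast on which bioequivalence is concluded. Zinc in MMN v CSB is the natural choice: it is the closest in composition and the only one near the stated power. Say that its co-nutrients are not identical to those of CSB. Report zinc only v CSB with its interval, state that it differs in both co-nutrients and delivery (Table 1), and state that failing to show equivalence there will not be read as evidence that sprinkles deliver zinc less well.

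The cost is wording in two sections, with no new arm, child or visit. The downside is a less favourable stated power for the zinc-only contrast.

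### The bioequivalence rule compares observed percentages with ±20 and does not require a confidence interval inside that margin, so as written it does not deliver the stated 5% significance

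*Protocol*

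**What the plan says.** The rule is near the end of Data analyses in the protocol: "Bioequivalence of sprinkles to CSB will be drawn if the percentages of children with serum zn" under 9.9 µmol/L falls within the ±20 rule, leaving out children with CRP above 10 mg/l. The protocol calls this "the basis to accept or reject the null hypothesis". The next sentence, which closes the section, reads "Significance will be determined at 95% confidence interval, P-value of 0.05". It comes after a list of chi-square tests, t-tests, ANOVA, ANCOVA and regressions, and it does not mention the ±20 margin.

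Section 3.4.6 (Sample size determination) attaches error rates to the equivalence claim: "To show equivalence within 20% rule with 80% power and 5% significance", giving 67 per group, or 80 after an attrition allowance. The margin enters the formula as 0.2, described as "20 % as per the bioequivalence rule". The planning values are given as follows: "The estimated post-intervention prevalence of 20%, 10%, 20% and 50% for the reference, ZN, ZN in MMN and MMN without ZN groups respectively".

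**The concern.** A rule that asks only whether two observed percentages lie within 20 of each other leaves sampling error out. When the true difference sits exactly at the margin, the observed difference falls on either side of it about equally often, so the false-equivalence rate there is near one half at any sample size. An equivalence test at 5% has to hold that rate to 5%, and it does so by requiring the whole interval, not just the estimate, to lie inside the margin.

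This is not a detail that a protocol would leave to the SAP. The protocol fixes the rule itself and names it as the basis for the primary conclusion. At stake is a claim that a powder is equivalent to CSB when its true deficiency rate is at or beyond the limit that the protocol calls unacceptable.

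**Working it through.** **Inputs.** From section 3.4.6: 67 evaluable children per group; margin 0.20; 5% significance and 80% power; expected prevalence 20% (CSB), 10% (ZN), 20% (ZN in MMN) and 50% (MMN without ZN). From Randomization: three villages per group. The ICC is not in the protocol; 0.01 and 0.05 are assumptions used only to show a range.

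**Step 1: the plan's own figure.** The printed formula gives (1.64 + 1.28)² × 0.71² / (0.2 − 1.0)² = 8.526 × 0.504 / 0.64 = 6.7, not 67. A standard two one-sided tests calculation with 20% in both groups comes close: 2 × 0.2 × 0.8 × (1.64 + 1.28)² / 0.2² = 0.32 × 8.526 / 0.04 = 68.2. Here 1.28 serves as the normal deviate for half of a 20% type II error. This is a reconstruction; the protocol does not say it was the method.

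**Step 2: chance of declaring equivalence, children treated as independent.** Let d be the observed difference in the proportion deficient. The written rule is |d| ≤ 0.20. The interval rules are |d| + z × SE < 0.20, with SE = √[p₁(1−p₁)/67 + p₂(1−p₂)/67] at the observed proportions and z = 1.645 (90% interval) or 1.96 (95% interval). Probabilities come from exact enumeration of two binomials with n = 67 and CSB at 20%.

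| True rate on the product | Written rule | 90% interval inside ±20 | 95% interval inside ±20 |
|---|---|---|---|
| 40% (at the margin) | 50.6% | 4.9% | 2.4% |
| 50% (no-zinc arm) | 10.5% | 0.2% | 0.1% |
| 20% (truly equal) | over 99% | 79% | 65% |
| 10% (ZN arm) | 95% | 51% | 39% |

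The first two rows are false claims of equivalence; the last two are power.

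**Step 3: hand check by normal approximation.** At 40% versus 20%, the mean of d equals the cut-off, so the pass probability is 0.50 whatever the SE. At 50% versus 20%, SE = √[(0.25 + 0.16)/67] = 0.078 and (0.20 − 0.30)/0.078 = −1.28, a pass probability of about 10%.

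**Step 4: sensitivity to sample size.** At 20% versus 40% the written rule passes 47% of the time with 54 per group and 53% with 80 per group. The 90% interval rule gives 4.8% to 4.9% at all three sizes.

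**Step 5: sensitivity to clustering (assumed ICC).** With about 67/3 = 22.3 children per village and an ICC of 0.05, the design effect is 1 + 21.3 × 0.05 = 2.07. At 50% versus 20%, SE = √(0.41/67 × 2.07) = 0.112 and (0.20 − 0.30)/0.112 = −0.89, a pass probability of about 19%. At the margin, simulation of three villages of 22 per arm gives 52% at ICC 0.01 and 51% at ICC 0.05. Clustering therefore does not cause the defect at the margin, but it raises the false-equivalence rate beyond it.

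**Step 6: power once villages are respected.** With the same three villages of 22 per arm and a 90% interval from village means on 4 degrees of freedom, simulated power at equal 20% rates is about 55%, 45% and 22% for an ICC of 0, 0.01 and 0.05. At 20% versus 10% it is about 39%, 34% and 22%.

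**The case against.** The strongest reply is that the sentence after the rule brings in a 95% interval and that section 3.4.6 attaches 5% significance to equivalence, so error control was intended. A reader might infer from the rule that no interval and no error rate were planned at all. The documents do not support that much. What they do support is that the interval is never tied to the ±20 margin, so the rule as written can be met by the point estimate alone. If the sponsor meant an interval inside the margin, the text has to say so and give the level.

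Three other strong readings also go too far.

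- **That a 95% interval belongs only to difference testing.** It does not. A 95% interval wholly inside ±20 is a valid and stricter equivalence rule, with a 2.4% pass rate at the margin. Choosing between 90% and 95% is a question of power, not of validity.
- **That the trial was certainly sized by two one-sided tests.** The Z of 1.64 and the closeness of 67 to 68 make this plausible, but the printed formula yields 6.7, so it remains an inference.
- **That ±20 might be a relative margin, 16% to 24% around a 20% reference.** The formula uses 0.2, and section 3.4.6 defines ε through absolute differences in proportions. That points to percentage points, and the unit should simply be written in.

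The objection that the repair costs more than a rewording is correct and is carried into the fix.

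**Conclusion.** The point holds: the primary decision rule is wrong as written. With 67 per arm and CSB at 20%, it declares equivalence for about 51% of products that are truly 20 points worse and about 10% of those 30 points worse. An interval rule at the 90% level would give 4.9% and 0.2%. The protocol states 5%.

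The figures assume that the rule is applied literally, that ±20 means absolute percentage points, that 67 children per arm are evaluable, and that children are independent. The result at the margin is insensitive to sample size and to clustering. The 19% for the 30-point case rests on an assumed ICC of 0.05. The conclusion is that the text does not require an interval within the margin, not that the sponsor intended no error control.

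**What to change.** Replace the rule in Data analyses with wording to this effect: equivalence of a powder to CSB is declared only if the two-sided confidence interval for the difference in the percentage of children deficient lies wholly within −20 to +20 absolute percentage points.

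- **State the level.** 90% corresponds to one-sided 5% tests, is consistent with the Z of 1.64 in section 3.4.6, and has about 79% unclustered power at equal 20% rates. 95% is also valid but stricter, with about 65%.
- **Use a standard error that allows for the randomised villages.**
- **Say what the 95% and P of 0.05 sentence covers.** Add that a non-significant difference test is not evidence of equivalence.

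The edit is a paragraph, but equivalence becomes harder to claim. The 80% power in section 3.4.6 should be restated: it is approached only at equal 20% rates with clustering ignored. At the protocol's own 20% versus 10%, the 90% interval gives about 51% unclustered, and less with three villages per arm. If the recalculated power is unacceptable, the number of villages or children needs to be reconsidered; keeping the present rule would not solve the problem.
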